### Secondary endpoints

Changes in the global score of Young Mania Rating Scale (YMRS, [45]) from baseline (V0) to visit 1 (at the end of the 8 week intervention (v1)Changes in the score of Clinical Global Impression CGI-BP [46] from baseline (V0) to visit 1;Changes in the score of the Hamilton Rating Scale for Anxiety HAM-A [47] from baseline (V0) to visit 1;Cognitive changes: changes at the end of the intervention will be assessed with the following measures:sustained and selective attentionworking memory and executive functionsperception of the attitude of mindfulness (Five Facet Mindfulness Questionnaire FFMQ, [48]) in patients in the experimental groupscales of social cognitionFunctioning: changes in total scale score of the Functioning Assessment Short Test (FAST; [49]).The following clinical variables are also assessed:Recurrence, defined as the emergence of a new acute episode whether depressive, mixed, hypo or manic at any time throughout the study, according to DSM-5 clinical criteria or when the score on the HDRS scale is ≥ 20 (depressive episode) or the Young scale ( YMRS ≥ 8) (hypo/manic episode), or a change drug or hospitalization is needed.Plasma levels of BDNF: changes from baseline to visit 1 (end of intervention).

Twenty-four weeks after the start of intervention following measurements are assessed: changes in the overall score of the Hamilton Depression Rating Scale (HDRS [44]), Young Mania Rating Scale (YMRS, [45]) from baseline (V0 ) to week 24 (V2) , Hamilton anxiety Scale HAM- A [47], CGI [46], general cognitive functioning, social cognition, functioning and biomarkers (BDNF).

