## Methods/design

This is a parallel 3-group, multicenter, prospective, randomized; single-blind (evaluator) controlled pilot trial, with a 4 month follow-up post-intervention. Patients diagnosed with bipolar disorder (BD) according to DSM −5 criteria for mild depression or subsyndromal depressive symptoms are assigned to one of the following 3 treatment groups: 1) psychopharmacological treatment *plus* Mindfulness Based Cognitive Therapy (MBCT); 2) psychopharmacological treatment *plus* a brief, structured group psychoeducation; 3) treatment as usual (TAU), defined as standard psychiatric care with standard pharmacologic treatment. After written informed consent is signed, patients meeting the inclusion criteria are randomized (2:2:1 ratio) through a Random Allocation Software. All three groups are assessed at baseline (t0), immediately after completing the program (t1; 8 weeks) and at follow-up six months after randomization. The assessments include the following variables: depression, manic and anxiety symptoms, general and social cognition, global functioning, BDNF, and other clinical variables. The evaluator who will collect the biomarkers and the clinical and psychometric data will be blind to allocation of treatment. The interrater variability between all researchers will be checked.

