### Primary outcome measures

Primary endpoint of the study is given by changes in the overall score of the Hamilton Rating Scale for Depression (HDRS [44]), from baseline (V0) to week 8 (v1) for each of the treatment groups.

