#### d) Mindfulness

Five Factors Questionnaire Mindfulness (FFMQ, [58]) 39 items assessing five mindfulness facets: observing, describing, acting with awareness, equanimity and no reactivity. Each item is scored on a Likert scale ranging from 1 (never) to 5 (very often). A high internal consistency and high predictive validity have been shown [58] and it has been uvalidated in Spanish [59].

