## Discussion

This study will provide feasibility information and preliminary effect size estimates to inform the effectiveness of adjunctive MBCT, adjunctive group psychoeducation and standard treatment on SS or mild depressive symptoms in BD. It is of interest to researchers involved in the development of new approaches to the treatment of residual affective symptoms and its negative impact in the course of illness. It can also provide information on variations of BDNF in the different treatment arms and on neuropsychological measures, which might suggest mechanisms of action and differences among treatments.

Strengths of the study include targeting a defined sample of bipolar patients with persistent depressive symptoms despite receiving a correct pharmacological treatment. This sample –as reported before- is representative of a high percentage of bipolar out-patients, who remain symptomatic more than one third of the time. The trial protocol was registered before randomization began (ClinicalTrials.gov: NCT02133170 Registered 04/30/2014) and was developed according to good clinical research practice enabling the randomized trial to be conducted with low risk of bias and a high degree of external validity. Both MBCT and psychoeducational interventions will be conducted using manuals and adherence to the treatment manuals will be tested. This makes it possible to implement the interventions in clinical practice, and the two interventions can be assessed in future trials. To standardize the application of MBCT and psychoeducation, specific training and meetings will be held. Specific training also may increase the inter-rater reliability on scales.

Since an 8-week psychoeducational program based in the Barcelona group-structured model has not proved effective neither in depressive symptoms nor in episode prevention, this could be a study weakness. But our objective is to compare MBCT versus an active psychosocial intervention, and this is the best model we could find. Sample size could also be a limitation, as well as the time of follow-up, especially regarding the possible effects on long-term course of BD.

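### The mindfulness questionnaire (FFMQ) endpoint is restricted to the MBCT arm, so it has no comparator, and as written the arm-specific form could disclose allocation to the blinded evaluator

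*Protocol article*

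**What the plan says.** The Secondary endpoints section has a group of cognitive measures for which "changes at the end of the intervention will be assessed with the following measures". One of them is the perceived "attitude of mindfulness (Five Facet Mindfulness Questionnaire FFMQ, [48]) in patients in the experimental" group. It is the only secondary measure in that list that is limited to one arm.

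Section d) Mindfulness describes the instrument as "39 items assessing five mindfulness facets: observing, describing, acting with awareness, equanimity and no reactivity". It gives the scoring, but it neither extends the form to the other arms nor says who administers it.

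Methods/design describes the trial as a "single-blind (evaluator) controlled pilot trial, with a 4 month follow-up post-intervention". It says "All three groups are assessed at baseline (t0), immediately after completing the program (t1; 8 weeks") and again at follow-up. The list of assessed variables that comes next does not name mindfulness. On blinding it says: "The evaluator who will collect the biomarkers and the clinical and psychometric data will be blind to allocation of treatment".

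The primary endpoint is "changes in the overall score of the Hamilton Rating Scale for Depression (HDRS [44]), from baseline (V0) to week 8 (v1"), so the HDRS is rated at the same visits that define the FFMQ change. The week-24 list under Secondary endpoints does not name the FFMQ.

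**The concern.** Two consequences follow from restricting a secondary endpoint to one arm of a three-arm randomized trial.

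**No comparator.** The stated aim is to compare MBCT with brief group psychoeducation. A before-after change in the MBCT arm mixes any effect of the training with repeat completion of the same questionnaire, expectation, the attention of a weekly group and improvement in mood. Psychoeducation has the same number of sessions and the same session length, so it is the arm that could separate the last three from the mindfulness content. It is left out.

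**A possible allocation cue.** The FFMQ is psychometric data, and the only statement on collection assigns psychometric data to the blinded evaluator. A form that exists for MBCT patients only would tell anyone who sees the assessment pack which patients had MBCT. The HDRS is rater-scored and the evaluator is the only party described as blinded, so a leak at that point would bear on the primary endpoint.

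**Working it through.** The article states no power, effect size or standard deviation for the FFMQ, so there is no figure of its own to reproduce. The check consists of counts and a comparison of sections.

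**Inputs.** Sample size 140 (Subjects); allocation 2:2:1 for MBCT, psychoeducation and TAU (Methods/design); two-sided 0.05 (Data analysis).

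**Arm sizes.**
- MBCT: 140 × 2/5 = 56
- Psychoeducation: 140 × 2/5 = 56
- TAU: 140 × 1/5 = 28

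**FFMQ data as written.**
- With FFMQ: 56 of 140 (40%)
- Without FFMQ: 56 + 28 = 84 of 140 (60%)
- Comparator observations: 0

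Data analysis applies a repeated-measures general linear model to the primary and secondary outcomes. With one arm measured, the FFMQ has no group factor to enter, and only a time effect within MBCT remains.

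**What the form would reveal if the evaluator saw it.** Form present means MBCT. Form absent means psychoeducation or TAU, without telling those two apart. Within the main contrast of 56 + 56 = 112 patients, that is enough to identify the arm of each one.

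**Which visits.** The endpoint is a change to the end of the intervention, so it needs V0 and V1. If the form were given at V0 to MBCT patients only, allocation would have to be known at V0. V2 is not affected as documented, because the week-24 list does not name the FFMQ.

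**What measuring all arms would give.** Detectable standardized difference d = (z0.975 + z0.80) × √(1/n1 + 1/n2). The 80% power is my assumption. Dropout, clustering within therapy groups and the gain from baseline adjustment are ignored.

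| Contrast | n | d at 80% power | Power at d = 0.30 | Power at d = 0.50 |
|---|---|---|---|---|
| MBCT vs psychoeducation | 56 vs 56 | 2.80 × √(1/56 + 1/56) = 0.53 | 35% | 75% |
| MBCT vs TAU | 56 vs 28 | 2.80 × √(1/56 + 1/28) = 0.65 | 25% | 58% |

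A comparison across all arms could thus detect a medium-sized difference from psychoeducation. As written, no difference can be estimated.

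**The case against.** The strongest defence has four parts.

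**The restriction may concern analysis and not administration.** Secondary endpoints says for whom the change is evaluated. Section d) has no arm restriction, and Methods/design says all three groups are assessed. Collecting the form from everyone and reporting it for MBCT alone would fit all three sections and would leak nothing. This reading is possible, but nothing states it: the one explicit sentence names the experimental group, and the general list of variables does not mention mindfulness. If it is what was meant, the comparator data would exist and only the endpoint wording and the analysis need changing.

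**The unblinding is inferred.** This stands in part. A reader might conclude that the restriction defeats evaluator blinding of the HDRS. The article does not support that, because it does not say who hands out, collects or sees the FFMQ, or in what order the assessments are done. Separate staff could administer it, or at V1 the HDRS could be rated before the form is seen. Such procedures are commonly left to the full protocol, so their absence is not the finding. What remains is that the article assigns psychometric data to the blinded evaluator and makes one psychometric form arm-specific, and these two statements sit badly together.

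**The FFMQ is not a declared mechanism outcome.** This stands. The Discussion does mention results "which might suggest mechanisms of action and differences among treatments", and a reader might take the FFMQ to be part of that. The subject of that sentence is BDNF and the neuropsychological measures. The FFMQ is listed only as a secondary cognitive measure, and the hypotheses in the Abstract do not include it. The point does not need the mechanism label.

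**It is a minor measure in a pilot, and a within-arm change can serve as a check that the skill was learned.** That is a legitimate limited use. Even so, without a comparator the change would not show that MBCT, and not time or group attention, produced it.

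**Conclusion.** The point holds in two parts of different strength.

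The lack of a comparator follows directly from the text: about 56 patients contribute, 84 do not, and the MBCT-versus-psychoeducation contrast cannot be made for the FFMQ. If the form is given as the endpoint is worded, no later analysis plan can recover the contrast, because the control data will not have been collected. The counts assume that the planned 140 are recruited and that the 2:2:1 ratio is met exactly.

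The threat to blinding is a risk as written. It would materialise only if the HDRS rater handles or sees the form, and as documented it concerns V0 and V1 only. The article does not establish that any patient would be unblinded.

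The change is worth making because it is cheap and resolves both parts. It is not a defect that by itself invalidates the primary endpoint.

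**What to change.** Remove the restriction to the experimental group. Give the FFMQ to all three arms at V0, completed before allocation, and at V1, in the same assessment pack for every patient. Specify the analysis as MBCT minus psychoeducation at week 8, adjusted for baseline FFMQ. Collection at V2 is optional, since the current week-24 list does not name the instrument.

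The cost is one 39-item form for the other 84 patients at two visits they already attend: 84 × 2 = 168 additional forms, with no extra visits. The main downside is the added patient burden.

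If the form must stay in one arm, the minimum is to have it collected by someone other than the HDRS evaluator, keep it out of that evaluator's sight, and describe the endpoint as a within-arm change only. That protects blinding but does not supply a comparator.

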### Intervention

MBCT program will be conducted in HULP by two experienced therapists with recognized expertise in Mindfulness based stress reduction (MBSR), MBCT and narrative psychotherapy. Both therapists will train two therapists from Vitoria with expertise in cognitive therapy and MBSR. The MBCT program consists of 8 weekly sessions of 90 minutes and will be performed in groups of approximately 10–15 patients. All therapy sessions will be audio recorded to be discussed and analyzed by the treatment team, in order to standardize the intervention. Treatment fidelity will be also assessed using the Mindfulness- based Cognitive Therapy Adherence Scale (MBCT-AS; [50]), which assesses the key constructs of MBCT during group sessions.

Psychoeducation program will be held in groups of 10 to 15 patients in 90-minute weekly sessions led by two therapists blind to the clinical and cognitive evaluation. The specific program of 8 sessions addresses disease awareness, adherence to treatment and early detection of prodromal symptoms. Homework will also be included. The program is based on the Psychoeducation Manual for Bipolar Disorder [51]. Attendance to at least 80% of the sessions of both interventions will be required to be considered complete.

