### Subjects

One hundred and forty bipolar out-patients with persistent mild/subsyndromal depressive symptoms will be recruited from Mental Health Centers as well as Private Psychiatric Clinics and Bipolar Patient Associations via announcements or physician referral. The study will be conducted in La Paz University Hospital (Madrid) and the Santiago Apóstol University Hospital (Vitoria).

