#### f) Biomarkers: serum analysis of BDNF

### Data analysis

An exploratory study of all collected variables identifies possible outliers and errors. The descriptive analyses of qualitative variables are expressed as frequencies and percentages and quantitative variables as mean, standard deviation, median and interquartile range. Analysis is performed by intention to treat. Comparison of qualitative variables between the intervention groups or between other factors of segmentation is by means of Chi 2 or Fisher ‘s exact test. For quantitative variables, the T-test, Mann -Whitney or Kruskal –Wallis and ANOVA are applied, depending on the normality of the variable (tested by Kolmogorov -Smirnov - Lilliefords). The change analyses along the track of the primary and secondary outcome variables are performed using a General Linear Model (ANOVA with repeated measures). Regression models are extracted to identify prognostic factors for the efficacy variables. The statistical package SPSS 18.0 is used in all tests and a bilateral level of p < 0.05 is considered statistically significant.

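### Both active arms are delivered in therapy groups, but every between-arm analysis named treats patients as independent; for any positive within-group correlation the type I error of MBCT versus psychoeducation exceeds 5%

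*Protocol article*

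**What the plan says.** The unit of randomization is the patient. Under Methods/design, "patients meeting the inclusion criteria are randomized (2:2:1 ratio) through a Random Allocation Software". Under Subjects, "One hundred and forty bipolar out-patients with persistent mild/subsyndromal depressive symptoms will be recruited".

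The Intervention section then places both active treatments in groups. MBCT is given in 8 weekly sessions of 90 minutes and "will be performed in groups of approximately 10–15 patients". For the comparator, "Psychoeducation program will be held in groups of 10 to 15 patients in 90-minute weekly sessions led by two therapists", also over 8 sessions. TAU is standard psychiatric care with no group component.

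The Data analysis section commits to specific methods. For comparisons between arms, "For quantitative variables, the T-test, Mann -Whitney or Kruskal –Wallis and ANOVA are applied", with chi-square or Fisher's exact test for qualitative variables. For the outcomes over time, "The change analyses along the track of the primary and secondary outcome variables are performed using a General Linear Model (ANOVA with repeated measures". The threshold is that "a bilateral level of p < 0.05 is considered statistically significant". No term for therapy group or therapist is named.

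The Abstract gives the aim as a comparison of MBCT with group psychoeducation and states a superiority hypothesis. The grouped arms are therefore the two arms of the main comparison.

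**The concern.** Patients who attend the same eight sessions share therapists, the other members and whatever happens in that group, so their outcomes may resemble each other more than those of patients in different groups. Each named between-arm method assumes that this resemblance is zero. Repeated-measures ANOVA does not help: it models the correlation between visits of one patient, not the correlation between patients in one group.

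If the correlation is positive, the variance of each active arm's mean is understated, p-values are too small and any confidence interval is too narrow. This affects the hypothesis test. It also affects the preliminary effect sizes that the Discussion offers as a product of the trial, because their stated precision would be too good.

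**Working it through.** **Inputs from the article.** Total 140 (Subjects); ratio 2:2:1 (Methods/design); group size about 10–15 in both active arms (Intervention); two-sided 0.05 (Data analysis).

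**Input assumed.** ICC for therapy group. The article gives none, so the range 0 to 0.10 is shown.

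**Arm sizes.** 140/5 = 28, so 56 MBCT, 56 psychoeducation, 28 TAU.

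**Number of groups.** 56/15 = 3.7 and 56/10 = 5.6. In whole groups that means four (14 each) or five (11.2 on average). Six would average 56/6 = 9.3, below the stated minimum.

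**The plan's own figure.** The only error rate stated is 5% two-sided. The unadjusted test returns it at ICC 0. The 140 cannot be reproduced, because the article gives no effect size, SD or power.

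**MBCT versus psychoeducation.** With group size m:

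- Design effect: DE = 1 + (m − 1) × ICC
- True error of the unadjusted test: 2 × [1 − Φ(1.96/√DE)]
- Effective n per arm: 56/DE

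Example, m = 15 and ICC 0.05: DE = 1 + 14 × 0.05 = 1.70; 1.96/√1.70 = 1.50; error = 13.3%; effective n = 56/1.70 = 32.9.

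| ICC (assumed) | DE, m = 10 to 15 | True SE / naive SE (√DE) | Effective n per arm | True error |
|---|---|---|---|---|
| 0 | 1.00 | 1.00 | 56 | 5.0% |
| 0.01 | 1.09–1.14 | 1.04–1.07 | 51–49 | 6.1–6.6% |
| 0.05 | 1.45–1.70 | 1.20–1.30 | 39–33 | 10.4–13.3% |
| 0.10 | 1.90–2.40 | 1.38–1.55 | 29–23 | 15.5–20.6% |

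**Simulation check.** Two arms of 56, in four or five groups per arm, 50,000 runs, no true difference. The higher figure in each pair for the unadjusted test is for four groups.

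| ICC | Unadjusted t-test | t-test on group means |
|---|---|---|
| 0 | 4.9–5.2% | 4.8–5.2% |
| 0.01 | 6.0–6.5% | 4.7–4.9% |
| 0.05 | 11.0–12.8% | 5.0% |
| 0.10 | 17.1–19.8% | 4.9% |

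An analysis that respects the groups holds the nominal level, even with so few of them.

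**MBCT (or psychoeducation) versus TAU.** Only one arm is grouped, so the variance ratio is V = (DE/56 + 1/28)/(1/56 + 1/28), which simplifies to (DE + 2)/3. At DE = 1.09, V = 1.03 and the error is 5.3%. At DE = 2.40, V = 1.47 and the error is 10.6%. At ICC 0.05 it is 6.8–7.8%.

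**The case against.** **No ICC is given, so the inflation is not established.** This stands. A reader might infer that the true error definitely exceeds 5%. The article does not support that: at ICC 0 the named tests hold their level, and at 0.01 the excess is one to two percentage points. The article also plans to limit differences between groups. Sessions are audio recorded and discussed, experienced MBCT therapists train those at the second site, MBCT fidelity is rated on a scale, and both arms follow manuals. These measures argue for the lower part of the range. They do not show that the correlation is zero, which is what the named analyses assume.

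**The groups may not be closed.** A reader may suppose fixed membership from an eight-session program, but the article does not say so. The point needs only shared sessions.

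**The top of the range is hard to reach.** With 56 patients, not every group can hold 15. Four equal groups of 14 give DE = 1 + 13 × 0.10 = 2.30 and an error of 19.6% at ICC 0.10, slightly under the tabulated 20.6%. The difference is small.

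**This is a pilot.** That lessens the weight of a significance error. It does not remove the point, because the article sets a hypothesis and a 5% threshold, and an effect size with overstated precision can mislead the next trial.

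**A condensed article leaves model detail to an analysis plan.** That would answer silence. Here the article names the model and the tests, and an analysis plan that followed them would carry the mismatch forward.

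**Conclusion.** The point holds, conditionally. The article describes group delivery in both arms of its main comparison and commits to between-arm analyses that ignore it. For any positive therapy-group ICC, the standard errors are too small and the type I error of MBCT versus psychoeducation is above the stated 5%: about 6–7% at an assumed ICC of 0.01, 10–13% at 0.05 and 16–21% at 0.10. Comparisons with TAU are affected less, about 5–11% over the same range. These figures assume a 56:56:28 split, groups of 10–15 and an ICC that the document does not supply.

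A reader might also infer that one good or bad group would bias the estimated effect. The documents do not support that either. Random group effects leave the expected difference unchanged, and each arm averages four or five groups; the precision is what is wrong.

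**What to change.** Record the therapy-group identifier for every patient in the two active arms. Replace the independence-based between-arm analyses of the primary and secondary outcomes with a partially nested mixed model: a random therapy-group effect in the MBCT and psychoeducation arms only, TAU patients entered as singletons, and Kenward-Roger or Satterthwaite degrees of freedom. Keep the within-patient correlation between visits in the same model. Report the ICC with its interval and describe it as imprecise, because four or five groups per arm cannot estimate it well. A group effect does not remove an effect of therapists common to all groups they lead, and the report should say so.

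**Cost.** One extra field on the case report form and revised analysis wording; no change to treatment, visits or sample size. Intervals widen and power falls. With four or five groups per arm there are 2 × (4 − 1) = 6 to 2 × (5 − 1) = 8 group-level degrees of freedom. By normal approximation, the standardized difference detectable with 80% power is (1.96 + 0.84) × √(2 × DE/56). This is 0.53 at ICC 0 and 0.64–0.69 at an assumed ICC of 0.05; the few degrees of freedom would raise the latter further. Most of that loss is already in the design if the correlation exists; the present analysis would not show it.
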